## Abstract

**Background:**

Sleep disturbances are very common in tinnitus sufferers with a high prevalence ranging from 50% to 77%. Untreated sleep disturbances and tinnitus can cause brain shrinkage and lead to cognitive impairments in late adulthood. Until now, non-pharmacological treatments are very few for older patients suffering from sleep disturbances and chronic tinnitus. Even though clinical trials of transcranial magnetic stimulation (TMS) have shown positive results in the treatment of either sleep disturbances or chronic tinnitus, the results are highly varied due to the superficial cortical target. Compared to TMS, focused low-intensity transcranial ultrasound stimulation (TUS) is a newly developed modality of non-invasive brain stimulation that offers promising therapeutic effects by transmitting acoustic energy into deep brain structures with a high spatial resolution (i.e., sub-millimeter), which sparks interest in managing the comorbidities in ageing populations.

**Methods and design:**

Chinese individuals between the ages of 60 and 90 years, who are right-handed and have sleep disturbances and chronic tinnitus, will participate in this pilot randomized clinical trial (RCT). Eligible participants will be randomly assigned to two treatment groups (1:1 ratio): low-intensity TUS or sham TUS (i.e., placebo-controlled group). Each group will consist of 15 participants. Before the treatment, high-resolution T1-weighted magnetic resonance imaging (MRI) data will be used to create a computational head model for each participant. The head model will help identify the treatment target of the left hippocampus. The treatments schedule contains six sessions of low-intensity TUS, three times per week, lasting two weeks. Each session of treatment lasts for 80 seconds. Throughout the study, outcome measurements will be conducted at four time points, including baseline, 2^nd^ week, 6^th^ week, and 12^th^ week. The primary outcomes include subjective sleep quality and severity of tinnitus. The secondary measurements include actigraphy, tinnitus handicap inventory and glymphatic function. Participants’ adherence to the program and any adverse event will be closely monitored throughout the duration of the clinical trial.

**Conclusions:**

It is expected that a 2-week treatment of low-intensity TUS will show significant enhancement in sleep quality and the severity of tinnitus symptoms compared to sham TUS. This proposed clinical trial will provide high-level and valuable clinical evidence that could inform the effect size and personalized modeling of focused low-intensity TUS for different types of brain diseases.

**Trial registration:**

ClinicalTrials.gov Identifier: NCT06776705.

## Introduction

Chronic tinnitus, as a common symptom, is the persistent perception of sound (e.g., buzzing or ringing) in the absence of external acoustic stimulus, lasting longer than six months [1]. The prevalence of chronic tinnitus rises steadily after age 40 and reaches 24% after age 65 [2,3]. Notable, chronic tinnitus can severely jeopardize sleep quality, brain health, and even lead to cognitive decline in aging populations [4–6]. The status of sleep disturbances is a frequent, but critical comorbidity in chronic tinnitus sufferers with a high prevalence ranging from 50% to 77% [7]. A growing body of data connects poor sleep quality to tinnitus and an increased risk of dementia in old adults [1,7]. Untreated sleep disturbances can cause glymphatic dysfunction and brain atrophy as a result of accelerated cognitive decline in chronic tinnitus sufferers [8–10]. Of note, glymphatic dysfunction can lead to the accumulation of neurotoxic waste products in the brain, potentially contributing to neurological conditions, such as tinnitus and cognitive decline. Poor sleep quality may exacerbate this dysfunction, creating a vicious cycle in which chronic tinnitus disrupt sleep, and sleep disturbances further compromise glymphatic clearance. Thus, targeting this cycle through interventions that address both sleep disturbances and chronic tinnitus could hold significant therapeutic value, particularly in ageing populations.

Understanding the neural underpinnings of the vicious cycle is fundamental to effectively managing co-occurring sleep disturbances and chronic tinnitus. Growing evidence indicates that the disruption of intrinsic neural networks can interfere with the brain activities tagged as default mode network (DMN), adding to sleep disturbances in chronic tinnitus sufferers [11]. DMN is an intrinsic brain network active during resting state and involved in mind-wandering and memory consolidation [12]. Neuroimaging studies found that sleep disturbances are closely related to the dysfunction of DMN. For example, people with sleep deprivation and insomnia showed weaker hippocampal-DMN connectivity [13] and smaller hippocampal volume [14]. It seems that enhancing sleep quality might be a feasible and indirect pathway for breaking down the vicious cycle and reducing the influence of chronic tinnitus on daily functioning. At present, non-pharmacological treatments are very limited for patients suffering from sleep disturbances and chronic tinnitus. With the advantage of targeting neural networks, non-invasive brain stimulation (NIBS), as a safe treatment, holds promise for managing these two conditions simultaneously. For example, clinical trials of transcranial magnetic stimulation (TMS) have been reported to improve the auditory processing, reduce the perception of tinnitus [15,16] and enhance the subjective sleep quality [17–19]. Although there are numerous studies that examine the effects of TMS in treating chronic tinnitus and sleep disturbances, the results are highly varied across the trials. The major reasons of heterogeneity might be summarized into the following three points: (1) Comorbidities: current clinical trials only focus on one symptom (i.e., either tinnitus or sleep disturbances) and provide insufficient evidence to support the use of TMS for managing both sleep disturbances and chronic tinnitus simultaneously. (2) Selection of treatment targets: TMS has very limited power to reach deep brain regions that might be related to sleep process, glymphatic system, and the perception of tinnitus, such as hippocampus. (3) Variability in head size and brain morphometry: the electric fields induced by TMS (i.e., dose) were severely affected by the morphometric features of the target at individual level [20]. Compared to TMS, focused low-intensity transcranial ultrasound stimulation (TUS) is a newly developed modality of NIBS that offers promising therapeutic effects by modulating the glymphatic system and transmitting acoustic energy into brain parenchyma [21,22]. Low-intensity TUS can reach deeper brain regions, such as hippocampus, with a high spatial resolution (i.e., mm) [23], which sparks interest in targeting DMN and managing the comorbidities in ageing populations.

Collectively, there is insufficient research data to support a large, full-scale randomized controlled trial (RCT) that involves investigation of the efficacy and sustainability of focused low-intensity TUS in patients with co-occurring sleep disturbances and chronic tinnitus. There is also a lack of clinical evidence that would allow the estimation of the efficacy of imaging-guided low-intensity TUS or sample size for the full-scale RCT. Thus, this pilot RCT aims to investigate the safety and feasibility of low-intensity hippocampal TUS for sleep disturbances in chronic tinnitus patients that allows to determine the sample size of a full-scale RCT. The findings of this RCT will provide valuable clinical evidence that could inform the effect size and personalized modeling of low-intensity TUS for age-related brain diseases.

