### Safety assessments

#### Adverse events checklist.

A checklist of adverse events associated with low-intensity TUS is applied to monitor tolerability and potential side effects. The Adverse Event Checklist (AEC) covering the symptoms from eight systems, including body as a whole, nervous system, cardiovascular, circulatory, digestive, musculoskeletal, urogenital systems and metabolic, is conducted at each assessment points through this pilot RCT [34].

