### Outcome measures

#### Primary outcomes.

Subjective sleep quality: The Pittsburgh Sleep Quality Index (PSQI), as a 19-item self-report questionnaire, is used to evaluate the subjective sleep quality in a month [27,35]. The PSQI contains seven components. The subscore of each component ranges from 0 to 3, and the maximum total composite score of the PSQI is 21. The sum of these component scores yields a measure of global sleep quality. The cutoff score of poor sleep quality is 5 or more.Severity of tinnitus: Tinnitus functional index (TFI) is a 25-item self-administered questionnaire which assesses eight domains of tinnitus impact, including intrusiveness; sense of control; cognitive; sleep; auditory; relaxation; quality of life (QoL); emotion [36]. The TFI Chinese version (TFI-CH) has been validated for clinical and research purposes in Hong Kong [37].

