### Statistical analysis

The data analyst will be blinded to the randomization of participants. Analyses will be primarily conducted by the intention-to-treat (ITT) approach. The measurement scales for primary and secondary outcomes are continuous. Linear mixed effect models will be used to evaluate the differences between the conditions on primary and secondary outcomes measured at each time point. This statistical method will facilitate the inclusion of the participants with missing data. For handling missing data, multiple imputation will be used in this study. Treatment, time points, and their interaction will be modelled as fixed effects. Participants will be modelled as random effects at each time point. Pre-treatment subjective sleep quality, tinnitus symptoms, and cognitive performance will be compared between the two randomized groups. Score changes of sleep quality and tinnitus symptoms from baseline to follow-up points across randomized groups will be tested with occasions (time points) at level one and participants at level two. Covariates, including age, duration of tinnitus and PSQI total score, identified from baseline differences will be entered in the regression model. Secondary analyses of groupwise differences in the changes of glymphatic function, hearing function, and their associations between changes of tinnitus symptoms and sleep quality will be performed. We will also monitor the incidence of adverse events and the characteristics of program adherence. Statistical significance will be set at 2-sided *p* < 0.05. Computations will be performed using R Studio (version 1.1.456).

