### Limitations

Although pilot RCT is essential for a full-size clinical trial, there are several key limitations that should be carefully considered when interpretating the results. First, pilot RCT involves a small sample size of participants which may reduce the statistical power. Second, the primary aim of pilot RCT is to test the feasibility of a novel treatment that has underpower to detect small but clinically meaningful effects. Third, this pilot RCT is an offline TUS treatment. Although pre-treatment simulation will be used for locating the target, no online EEG or fMRI will be applied for verifying whether TUS actually modulates the hippocampus. Fourth, objective assessment of hearing function was not included in this study. Fifth, the sample size calculation was based on a medium effect size (0.5) without prior TUS data. Due to the limited sample size, the results may not be generalizable to larger populations. Their limitations highlight the need for cautious interpretation and proper planning for subsequent full-scale clinical trials.

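### The stated aim is safety and feasibility, but no ranked outcome measures either, and the only adverse-event checklist described is not tied to the treatment sessions

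*Protocol article*

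**What the plan says.** **Aim.** The Introduction states that "this pilot RCT aims to investigate the safety and feasibility of low-intensity hippocampal TUS for sleep disturbances in chronic tinnitus patients", and the sentence continues "that allows to determine the sample size of a full-scale RCT". The Limitations section repeats that "the primary aim of pilot RCT is to test the feasibility of a novel treatment".

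**Outcomes.** The Abstract says "The primary outcomes include subjective sleep quality and severity of tinnitus". The Outcome measures section names the two instruments: "The Pittsburgh Sleep Quality Index (PSQI), as a 19-item self-report questionnaire, is used to evaluate the subjective sleep quality in a month", and "Tinnitus functional index (TFI) is a 25-item self-administered questionnaire which assesses eight domains of tinnitus impact". The secondary outcomes are actigraphy, the THI and the DTI-ALPS index of glymphatic function.

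**Safety and adherence.** The Safety assessments section says that the Adverse Event Checklist "is conducted at each assessment points through this pilot RCT". The Assessment schedule puts adverse events at one week before treatment (T0) and at weeks 2, 6 and 12 (T1 to T3). The Statistical analysis section adds: "We will also monitor the incidence of adverse events and the characteristics of program adherence". The Abstract promises that adherence and any adverse event will be watched closely for the whole trial.

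**Treatment.** There are six sessions, three a week for two weeks (Grouping and treatment schedule).

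**The concern.** A pilot's outcome list should mirror its aim, because the ranked outcomes decide what is analysed and reported first. Here the declared aim has no ranked outcome. As written, the main result will be a PSQI and TFI comparison tested at two-sided 0.05, which the Limitations section itself calls underpowered. Safety and feasibility would be reported as by-products.

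The second issue is data capture. If safety is an aim, its main instrument should be used close to the exposure. The checklist described is given before the course and then not until week 2. A short-lived symptom after session one or two could be forgotten or misdated by then. What is at stake is how complete the safety record is, and that record is one of the two things the pilot says it is for.

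**Working it through.** The core of this point is a comparison of passages. The arithmetic only gives context.

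**Step 1: aim against outcomes**

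| Item | Where stated | Safety or feasibility measure? |
|---|---|---|
| PSQI (primary) | Abstract; Outcome measures | No: efficacy |
| TFI (primary) | Abstract; Outcome measures | No: efficacy |
| Actigraphy (secondary) | Abstract; Outcome measures | No: efficacy |
| THI (secondary) | Abstract; Outcome measures | No: efficacy |
| DTI-ALPS (secondary) | Abstract; Outcome measures | No: mechanistic |
| Adverse events | Safety assessments; Statistical analysis | Yes, but unranked |
| Adherence | Abstract; Statistical analysis | Yes, but unranked |

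None of the five ranked outcomes addresses safety or feasibility.

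**Step 2: what the sample size is argued from**

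The Sample size section calls the number suitable for the primary aims, then derives it from potential efficacy at a standardised effect of d = 0.5: 13 per group, raised for 10% dropout.

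- Dropout step: 13 / (1 − 0.10) = 14.4, rounded up to 15 per arm, 30 in total. This reproduces the plan.
- The 13: n per arm = 2(z/d)². With z = 1.282 (two-sided 80% interval), 2 × (1.282/0.5)² = 13.1, which is close to the plan. With z = 0.842 (one-sided 80%, the label the plan uses), 2 × (0.842/0.5)² = 5.7, which is not. The label deserves a check, but that is a separate matter.
- Power at two-sided 0.05 with 15 per arm, normal approximation: Φ(0.5 × √(15/2) − 1.96) = Φ(−0.59) = 28%. The t-test gives 26%. For 80% power, n = 2 × (1.96 + 0.842)² / 0.5² = 62.8, so 63 per arm (64 by t-test).

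The size is therefore argued from efficacy too, at a number that supports estimation and not a verdict on efficacy.

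**Step 3: checklist timing against treatment**

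| Scheduled checklist | Position relative to the six sessions |
|---|---|
| T0 | One week before treatment |
| T1, week 2 | End of the two-week course |
| T2, week 6 | After the course |
| T3, week 12 | After the course |

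This assumes that weeks are counted from the start of treatment, as the schedule implies. None of the four administrations is tied to a session, and the first after treatment starts is at week 2. The recall period for session one is then up to about two weeks. The Randomization section keeps the treating researcher out of assessments, so the article names nobody who records symptoms at sessions.

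**Step 4: the two monitoring statements**

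The Abstract's whole-trial monitoring and the visit-based checklist can both be true only if there is some further route for capturing events. The article describes none.

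**The case against.** **The aim is wider than safety and feasibility.** The same sentence in the Introduction adds sizing the full trial, and PSQI and TFI data serve that. This stands. It is a good reason to keep both scores, but it does not explain why the other two parts of the aim are unranked.

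**Adverse events are not confined to visits.** A reader might infer that events are checked at assessment visits and nowhere else. The Abstract says otherwise, the SPIRIT schedule in Fig 1 is not available here, and a journal article often leaves operational capture to the full protocol. The supportable statement is narrower: the only checklist described is visit-based, and it needs reconciling with the Abstract.

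**The pilot can still report on its aim.** A reader might conclude that it cannot. Adverse events and adherence are collected and can be described, so that goes too far. Missing progression criteria may be condensation and are not counted.

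**Checklist content.** The eight body systems named include no ear or scalp heading, and a reader might infer that such symptoms are not asked about. The individual items are in a cited source that is not shown, and a general heading could cover them. This is a point to confirm, not a defect.

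**The trial is under way.** Study timeline gives a start in January 2025, with fourteen eligible participants screened and scanned by the end of February. Removing both registered primary outcomes now would be hard to defend. This also stands, and the fix keeps them as the efficacy outcomes.

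**Conclusion.** The point holds as a mismatch that should be corrected; it does not invalidate the trial. None of the five ranked outcomes measures safety or feasibility, although the Introduction and Limitations make these the aim. None of the four scheduled checklist administrations is tied to any of the six sessions, although the Abstract promises monitoring throughout.

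The effect on the safety data cannot be given as a number. It depends on how many transient symptoms occur and are forgotten, and the document has no figure for either. That recall would lose some of them is a reasonable inference, and it assumes no undisclosed per-session record.

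A reader might offer binomial limits as the size of the problem: no events in 15 active participants leaves a two-sided upper 95% limit of 1 − 0.025^(1/15) = 22%, and an illustrative 27 of 30 retained has an exact interval of 73% to 98%. These are correct, but they follow from 30 participants and would be the same after the fix. Nor is the 10% dropout figure a feasibility target: the plan uses it only as a sample-size allowance, and an interval of that width could not judge it.

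**What to change.** 1. **Give safety and feasibility outcome status**, by dated amendment before unblinding, ranked to match the stated aim:
   - participants with any treatment-emergent adverse event, by arm;
   - sessions completed out of six, for example as the proportion completing all six;
   - retention at week 12.

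   Report each with an exact confidence interval, without a pass mark taken from the dropout allowance.
2. **Keep PSQI and TFI as the efficacy outcomes**, reported as between-arm estimates with confidence intervals to inform the full trial.
3. **Reconcile the Abstract with the Safety assessments and Assessment schedule sections.** Have participants complete the existing checklist themselves at each of the six sessions as well as at the assessment visits. Self-completion keeps the treating researcher from rating events.
4. **Confirm three practical points:** that the checklist suits self-completion; that it covers ear or hearing and scalp symptoms (the Limitations section says that hearing is not objectively assessed); and who receives the session forms, since the Discussion says that assessors have no contact with participants during treatment.

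The cost is a few minutes at six visits that already take place, plus an ethics and registry amendment. Participants treated before the change will lack session-level records, and the report should say so.

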## Materials and methods

### Research design

A two-arm RCT will be carried out with repeated measurements, including baseline, 2^nd^ week, 6^th^ week and 12^th^ week. It makes reference to the suggested requirements of a phase II design for non-pharmacological intervention. The study will be conducted following the Recommendations for Interventional Trials (SPIRIT) (Fig 1) and the Consolidated Standards of Reporting Trials (CONSORT) statement (http://www.consort-statement.org) (Fig 2).

**Fig 1 pone.0329950.g001:**
[figure not shown]
Schedule of the pilot randomized clinical trial according to the standard protocol items: Recommendations for interventional trials checklist (SPIRIT). Abbreviations: TUS = Transcranial ultrasound stimulation.

**Fig 2 pone.0329950.g002:**
[figure not shown]
The Consolidated Standards of Reporting Trials (CONSORT) flow diagram for the clinical trial of focused low-intensity hippocampal transcranial ultrasound stimulation (TUS).

### Sample size and power analysis

Until now, no published clinical trials have been conducted in chronic tinnitus patients with sleep disturbances, thus our calculation will be based on published data in similar populations. As this clinical trial is a pilot and feasibility study, the sample size is considered fifteen older patients suffering from sleep disturbances and chronic tinnitus in each study arm. This sample size is appropriate for the primary study aims. To evaluate the potential efficacy of the treatments as compared with the control and assuming a medium standardised effect size (0.5), thirteen participants are required in each group with 80% one-sided CI approach which is suggested for pilot trials [24]. Besides, the sample size in this study is also estimated based on our recent pilot study using transcranial random noise stimulation (tRNS) to treat sleep disturbances (n = 13 for each arm) [25]. Thus, to account for the dropout rate of 10%, the total sample size is calculated as thirty.

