### Randomization, allocation and masking

To ensure the homogeneous distribution between groups, all the eligible participants will be randomly assigned to receive either low-intensity TUS or sham TUS following a 1:1 ratio. A randomization assignment will be generated prior to study enrollment using an online system (http://randomization.com/) by a statistician who is not involved in the study design. After the randomization and baseline assessment, the participants will be scheduled for treatment sessions. Assessment staff and participants will be blinded to the study design and group allocation. The researcher who administers the TUS treatment will not participate in the assessments.

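### Thirteen per group does not follow from the stated 80% one-sided CI criterion (which needs about 6–7), and the analysis then uses a two-sided 5% test for which the trial was not sized

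*Protocol article*

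**What the plan says.** In the protocol article, Sample size and power analysis gives the basis for the trial's size. It works from "assuming a medium standardised effect size (0.5") and states that "thirteen participants are required in each group with 80% one-sided CI approach which is suggested for pilot trials". It adds a precedent, the team's earlier pilot of random noise stimulation to "treat sleep disturbances (n = 13 for each arm"). It then says that "to account for the dropout rate of 10%, the total sample size is calculated as thirty". Randomization, allocation and masking has participants "randomly assigned to receive either low-intensity TUS or sham TUS following a 1:1 ratio", so the plan is 15 per arm.

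Statistical analysis does not mention the 80% interval. It plans linear mixed models and says "Statistical significance will be set at 2-sided" p < 0.05.

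The abstract's conclusions expect that two weeks of treatment "will show significant enhancement in sleep quality and the severity of tinnitus symptoms compared to sham TUS". The Introduction gives the aim as a safety and feasibility study "that allows to determine the sample size of a full-scale RCT". Limitations says in general terms that a small sample may lower power, but names the shortfall only for small effects that would still matter clinically.

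**The concern.** The sample-size sentence contains every input needed to check it: effect size, confidence level, sidedness and number per group. Put together in the usual way, they give about half the stated number. A reader cannot tell whether the trial was sized on a one-sided 80% limit, a two-sided 80% interval, or a total written as a per-group figure.

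The second issue is that the rule used to size the trial is not the rule named for the analysis. An 80% interval is a lenient criterion suited to a pilot, and a two-sided 5% test is a much stricter one. If the medium effect assumed for sizing is real, a non-significant result is still the more likely outcome under that test across the correlations examined below up to 0.7. A reader told to expect a significant benefit could then take such a result as evidence against the treatment.

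**Working it through.** **Inputs from the protocol article.** Standardised effect d = 0.5; 80% one-sided CI; 13 per group; 10% dropout; 30 in total (all from Sample size and power analysis); 1:1 allocation (Randomization, allocation and masking); two-sided 0.05 (Statistical analysis).

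**Assumption.** No formula is given and the cited method source is not at hand. The usual form is taken: with an observed difference of zero, the one-sided limit must exclude d. This gives n per arm = 2 × (z/d)², or, with t quantiles, the smallest n for which t(2n−2) × √(2/n) ≤ d.

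**Step 1: the stated criterion (80% one-sided, z = 0.8416).**
- Normal: 2 × (0.8416/0.5)² = 2 × 2.833 = 5.67, so 6 per group.
- t: at n = 6, 0.879 × √(2/6) = 0.507, which is too wide. At n = 7, 0.873 × √(2/7) = 0.467, which is enough. So 7 per group, or 13 in total if the arms may differ by one.
- The stated figure of 13 per group is not reproduced.

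**Step 2: which changes to the wording give about 13.**
- 80% two-sided, equal to 90% one-sided (z = 1.2816): 2 × (1.2816/0.5)² = 13.14, so 14 per group after rounding up, and also 14 by t.
- 80% one-sided by t, with the unit read as the total: 13 in total.
- Reading 80% as power does not help. With one-sided alpha 0.20, 2 × [(0.8416 + 0.8416)/0.5]² = 22.7, so 23 per arm. With two-sided alpha 0.20 it is 37 per arm.

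**Step 3: what 13 evaluable per group delivers (√(2/13) = 0.392).**
- 80% one-sided: 0.8416 × 0.392 = 0.330 SD (0.336 by t).
- 80% two-sided: 1.2816 × 0.392 = 0.503 SD (0.517 by t), just short of excluding 0.5.

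**Step 4: dropout.** 13/0.9 = 14.4, so 15 per arm and 30 in total. This step reproduces, so the fault is confined to the sentence about the criterion.

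**Step 5: the analysis rule (two-sided 0.05, d = 0.5, unadjusted comparison at one time point, noncentral t).**

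| | 13 per arm | 15 per arm |
|---|---|---|
| Power | 23.2% | 26.2% |
| Power, normal approximation | 24.7% | 27.7% |
| Observed d needed for p < 0.05 | 0.81 | 0.75 |
| True d detectable with 80% power | 1.15 | 1.06 |

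Reaching 80% power at d = 0.5 would take 64 per arm (63 by the normal approximation).

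**Step 6: sensitivity to baseline adjustment.** The document gives no baseline-to-follow-up correlation r, so r is assumed. If 0.5 is in units of the raw outcome SD, adjustment replaces d by 0.5/√(1 − r²).

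| Assumed r | 13 per arm | 15 per arm |
|---|---|---|
| 0.5 | 29.3% | 33.3% |
| 0.7 | 40.3% | 45.7% |
| 0.9 | 80.1% | 85.8% |

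**The case against.** Four points can be made for the plan.

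- **The formula is the reviewer's.** This is correct, and it is why the result is stated under an assumption. A reader might infer that no reading gives 13. That goes too far: changing the sidedness gives 13.14 per arm, and changing the unit gives 13 in total. What stands is that the sentence as written, taken in the usual way, does not give 13 per group. The earlier pilot with 13 per arm is a precedent and does not supply the missing calculation.
- **The error is in the safe direction.** This stands. Fifteen per arm more than meets an 80% one-sided criterion. A reader might infer that the trial is too small for its stated criterion, and the document does not support that.
- **Low power in a pilot is not a fault, and it is partly disclosed.** This also stands in the main. The article describes a pilot and feasibility study, claims 80% power at two-sided 5% nowhere, and advises caution in Limitations. But that section names the shortfall only for small effects, whereas the low power applies at the medium effect used for sizing, and the abstract still expects a significant result.
- **The planned mixed model is not an unadjusted t test.** This stands, so 23–26% must not be presented as the power of the planned analysis. Averaging the three follow-ups as well would raise it further, to about 47–54% at r = 0.5 and 59–66% at r = 0.7. That assumes equal correlations and the same effect at each visit, while the plan speaks of differences at each time point.

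A reader might also infer that the full-scale trial will be sized on an exaggerated effect. That would require sizing it only after a significant pilot result, and the article states no such rule. Without that selection, the observed effect is close to unbiased.

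**Conclusion.** The point holds as a defect of justification and consistency, not as a shortage of participants. Under the usual CI approach, the stated inputs give 6–7 per group against the stated 13. The number can be explained only by changing the sidedness or the unit, and the document does not show which was meant.

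The two-sided 5% rule is not the rule the trial was sized on. At d = 0.5, its power is about 23–26% unadjusted at one time point, or about 29–46% with baseline adjustment at an assumed correlation of 0.5–0.7. The first range rests on the protocol's own effect size. The second also rests on an assumed correlation and on 0.5 being in raw SD units. Neither supports the abstract's expectation of a significant benefit.

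**What to change.** 1. Correct the sample-size sentence to whichever criterion was actually used, and state the formula:
   - an 80% two-sided (90% one-sided) interval, needing 14 per group, which the 15 enrolled meet; or
   - an 80% one-sided interval, needing 6–7 per group, with 13 evaluable per group excluding about 0.33 SD.

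   Under the first option, 10% dropout leaves 15 × 0.9 = 13.5 per group. The text should therefore add that with 13 evaluable the limit lies at 0.50–0.52 SD, and should not claim that 0.5 is strictly excluded.
2. In Statistical analysis, report the PSQI and TFI treatment effects with that same interval and label p < 0.05 as exploratory.
3. State the approximate power at an effect of 0.5 under two-sided 5%, with its assumptions, and extend the caution in Limitations from small effects to the assumed medium effect.
4. Soften the abstract's expectation of a significant benefit over sham.

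The cost is wording in four places. No extra participants are needed; the only downside is that the stated claims become less favourable.
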